### Statistical plan

2.6

Continuous variables will be presented as mean ± SD or median (interquartile range—IQR) as appropriately; categorical variables as percentages. All statistical comparisons will be made under the intention‐to‐treat principle. A repeated‐measures analysis of variance (ANOVA) will be used for the comparisons of continuous outcomes among the two‐intervention groups. The interaction group*time‐points will be tested to unveil any effect of time (15 and 30 days) on the magnitude of the intervention. Only in the event of imbalance in baseline characteristics, repeated‐measures analysis of covariance (ANCOVA) will be used. A two‐sided *P*‐value of <0.05 will be considered to be statistically significant for all analyses. All analyses will be performed with Stata 14.1.

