### Sample size calculation

2.5

The null hypothesis of the study is that the mean peakVO2 absolute differences from baseline to 15 days after the withdrawal of beta‐blockers will be similar. The sample size determination for this study assumes two‐sided testing at the 0.05 significance alpha level. Because this is a randomized clinical trial, we assume no differences in peakVO2 at baseline among the two arms. Based on a prior study of our group in HFpEF, we assume eligible patients will have a mean (SD) peakVO2 of 10 ± 2.8 mL/kg/min.^8^ Along the same line, and based on prior studies about the deleterious effects of heart rate slowing in HFpEF patients, we speculate a blocker withdrawal will increase peak VO2 about 10%. With this data in mind, we assume a mean change of 1.2 mL/kg/min and a common SD of 2.0,^8^, ^25^, ^26^ a clinical meaningful change according a recent HFA position paper that consider significant clinical changes of peakVO2 those greater than 6% when baseline peakVO2 is lower than 14 mL/min/1.73 m^2^.^27^

Assuming an allocation ratio of 1:1, a total of 42 patients (21 patients per group) would provide 90% of power at a significance alpha level < 0.05. Assuming 20% of withdrawals or losses to follow‐up, a total of 26 patients per arm (52 patients) will be enrolled. The software used for sample size calculation was “xsampsi” from Stata 14.1.

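### Intention-to-treat is promised, but a repeated-measures ANOVA run on days 15 and 30 takes its treatment effect only from patients with both tests

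*Protocol article*

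**What the plan says.** Section 2.6 (Statistical plan) sets the principle: "All statistical comparisons will be made under the" intention-to-treat principle. It then fixes the model for continuous outcomes, a repeated "measures analysis of variance (ANOVA) will be used for the comparisons of continuous outcomes among the" two intervention groups. The only time points it names are those of the group-by-time interaction, which is to reveal "any effect of time (15 and 30 days) on the magnitude of the intervention". ANCOVA is reserved for baseline imbalance.

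Section 2.5 (Sample size calculation) states that "a total of 42 patients (21 patients per group) would provide 90% of power". It continues "Assuming 20% of withdrawals or losses to" follow-up, so that "a total of 26 patients per arm (52 patients) will be enrolled".

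The Introduction defines the primary endpoint as the change in peakVO2 at 15 days. Section 2.4.1 gives each patient three exercise tests: baseline, day 15 and day 30. Treatment switches after day 15 in both arms (Section 2.3.2).

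**The concern.** In this two-period crossover, the within-patient treatment effect is a contrast between day 15 and day 30. A patient who has baseline and day 15 but not day 30 was randomised, was treated as allocated and was tested at the time the primary endpoint names. An ANOVA on the two post-randomisation values cannot use that patient for the contrast. The result would be an analysis of those who completed both periods, reported under an intention-to-treat label.

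Two things are at stake: whether the analysed population is the randomised one, and whether the estimate is biased if those who leave after day 15 differ in response from those who stay. Patients know whether they are taking the beta-blocker, so loss related to response is possible. The article does not say that it will happen.

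**Working it through.** **Inputs.** From the article: 52 enrolled, 42 needed, 20% losses, effect 1.2, SD 2.0, baseline SD 2.8 (Section 2.5); time points 15 and 30 days (Section 2.6). Assumed: 2.0 is the SD of within-patient differences, since the article does not say which SD it is; SD 2.8 holds at every visit; correlations between visits are equal. Then 2.0² = 2 × 2.8² × (1 − ρ), so ρ = 1 − 2/7.84 = 0.745.

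**1. The plan's loss allowance.** 42/0.8 = 52.5 and 52 × 0.8 = 41.6. So 52 enrolled leaves about 42, and about 10 are lost. The split between loss before and after day 15 is not given, so 0 to about 10 patients have exactly one period. Whether 42 follows from the stated effect and SD is a separate question.

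**2. Who enters the contrast.** With d = (day 15 − day 30) for each patient, the estimate is (mean d in arm A − mean d in arm B)/2. A patient without day 30 has no d. Keeping that patient's row in long format with a patient factor does not help, because the patient's own term absorbs the single value. In 400 simulated trials the long-format ANOVA and the complete-pairs estimate agreed to about 1e-13.

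**3. Precision, if all 10 losses fall after day 15 (5 per arm).**
- Complete pairs: variance = (2.0²/4) × (2/21) = 0.0952, SE 0.309.
- Single-period patients compared between arms: variance = 2 × 7.84/5 = 3.136.
- Combined, as in a mixed model without baseline: 1/(10.5 + 0.319) = 0.0924, SE 0.304, about 3% less variance.
- Power, Φ(effect/SE − 1.96): 97.3% against 97.7% at 1.2; 90.0% against 90.8% at 1.0.
- At correlations 0.3, 0.5 and 0.9 the SE falls from 0.511 to 0.491, 0.432 to 0.420, and 0.193 to 0.192.

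With baseline added, simulated SDs under random loss fell from 0.310 to 0.297 in one set of runs and from 0.321 to 0.307 in another, about 8% less variance in each.

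**4. How bias arises.** The within-patient error variance is 2. If loss depends on the change from baseline to day 15 (variance 2 + 2 = 4), half of any selection on that change is day-15 error (2/4). The contrast halves it again. If the retained arm-A patients average m below their arm's mean change, and arm-B loss is unrelated to response, the estimate shifts by −m/4. A result of 1.05 corresponds to m = 0.60, and 1.00 to m = 0.80.

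**5. Simulations** (52 patients, true effect 1.2, SD 2.8, correlation 0.745). The loss rules are assumptions and differed somewhat between sets of runs; where recorded, 20% to 25% were lost.

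| Assumed loss after day 15 | Both tests only | All values with baseline |
|---|---|---|
| Arm-A patients who improved leave more often | 0.96 to 1.05 | 1.20 to 1.21 |
| Patients doing worse at day 15 leave | 1.14 to 1.15 | 1.20 to 1.21 |
| Loss of 38% if day-15 value under 10, else 5% (200 trials) | 1.20 | not run |

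In the last row a mixed model without baseline gave 1.21; the Monte Carlo error is 0.298/√200 = 0.021. Loss tied to the day-15 level by the same rule in both arms largely cancels.

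**6. What does the correcting.** One set of runs used two response-related loss rules and compared the models directly. Both tests only gave 1.14 and 1.00. A mixed model on days 15 and 30 alone gave 1.16 and 1.06. A mixed model with baseline gave 1.19 and 1.20. An ordinary patient-factor ANOVA with baseline as a third level matched the last.

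**The case against.** The strongest reply is that the text does not exclude baseline. Section 2.6 mentions 15 and 30 days when describing the interaction test; it does not list the model's responses. The endpoint is a change from baseline, and if baseline were a third level in a long-format ANOVA, a patient with baseline and day 15 would still count. This stands. The exclusion follows from the time points named, not from the label ANOVA, so a reader who infers that the named method must discard these patients goes further than the text.

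Three other inferences are tempting and not supported.
- **That the whole 20% is dropped.** The article gives no timing. Patients lost before day 15 have no first-period result for either model to use.
- **That the stability condition in Section 2.3.2 makes loss informative.** It governs the dose steps. The article does not say that unstable patients leave or go untested.
- **That the trial is underpowered by this.** Enrolment already allows for the losses.

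It can also be said that missing-data handling belongs to an analysis plan not shown here, and that intention-to-treat does not by itself prescribe a method. That is fair for a missing rule. Here, however, the article states principle, model, time points and loss rate together, and on their plain reading they do not fit.

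Finally, the larger bias figures need improved arm-A patients to leave preferentially, which nothing in the article suggests. Loss of patients doing worse shifts the estimate by only about 0.05, one sixth of the SE of 0.309.

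**Conclusion.** The point holds in a limited form and merits a change of wording. Run on the two time points that Section 2.6 names, the ANOVA takes the within-patient effect only from patients with both tests, leaving out 0 to about 10 of 52 who may have usable baseline and day-15 data. The cost in power is under 1 point in the main case. The possible bias runs from none (random loss) through about 0.05 to about 0.2 mL/kg/min of a true 1.2, depending wholly on assumed loss mechanisms. These sizes also rest on reading 2.0 as the SD of differences and on equal correlations between visits. The remedy that matters is using every available value, baseline included, as a response; REML is a convenient way to do so and not itself the cure.

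**What to change.** In Section 2.6, name as the primary analysis of continuous outcomes a linear mixed model fitted by REML. Its responses are the baseline, day-15 and day-30 values of every randomised patient, with fixed effects for time point (period) and treatment and a random patient effect. Keep the repeated-measures ANOVA on patients with both tests as a sensitivity analysis, and report how many patients it leaves out and when they were lost.

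The cost is revised wording and slightly more analysis work. No new data or patients are needed, and Stata 14.1, already named, fits the model. The downside is a missing-at-random assumption: the model handles loss that depends on observed baseline and day-15 values, but not loss that depends on unobserved ones.

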**Methods:**

This is a prospective, crossover, randomized (1:1) and multicenter study. After randomization, the clinical and cardiac rhythm will be continuously registered for 30 days. PeakVO2 is assessed by cardiopulmonary exercise testing (CPET) at 15 and 30 days in both groups. Secondary endpoints include quality of life, cognitive, and safety assessment. Patients with stable HFpEF, functional class New York Heart Association (NYHA) II‐III, chronic treatment with beta‐blockers, and ChI will be enrolled. A sample size estimation [alfa: 0.05, power: 90%, a 20% loss rate, and delta change of mean peakVO2: +1.2 mL/kg/min (SD ± 2.0)] of 52 patients is necessary to test our hypothesis.

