## INTRODUCTION

1

Heart failure (HF) with preserved ejection fraction (HFpEF) is a heterogeneous syndrome that is the predominant form of HF in western countries.^1^, ^2^, ^3^, ^4^ Chronotropic incompetence (ChI), defined as the inability to increase heart rate during exercise adequately, is commonly present (ranging from 20 to 75%) in HFpEF patients.^5^, ^6^, ^7^, ^8^, ^9^, ^10^, ^11^ Furthermore, ChI has been proposed as a pathophysiologic mechanism associated with poorer outcomes and decreased functional capacity in a subgroup of patients with HFpEF.^8^, ^12^, ^13^

Data from current registries show a high proportion (ranging from 50% to 80%) of beta‐blockers prescription in HFpEF patients regardless of the heart rhythm.^3^, ^14^ Nevertheless, there is no well‐established evidence endorsing the effect of beta‐blockers. For instance, recent studies suggested that patients with an ejection fraction of 50% or greater did not see any benefits from receiving beta‐blockers.^15^, ^16^, ^17^ Even more, the evidence is missing stratifying patients with HFpEF across ChI status.

When ChI is present, beta‐blockers may have negative effects on functional capacity and other surrogates of the disease severity by exacerbating the ChI. Thus, we hypothesize that deprescribing beta‐blockers in this particular scenario will translate into an improvement in short‐term maximal functional capacity. The purpose of this randomized controlled study is to evaluate the short‐term effects of beta‐blockers withdrawal on the functional capacity, cognitive function, and quality of life (QoL) in patients with HFpEF and documented ChI.

The primary endpoint of the study is absolute and relative changes in peak oxygen uptake (peakVO2) at 15‐day after the intervention. The secondary endpoints are: (a) 15‐day absolute changes in cognitive function assessed by the Mini‐Mental State Examination (MMSE) and Montreal Cognitive Assessment (MoCa); (b) 15‐day absolute changes in echocardiogram parameters (E/E' ratio and left atrial volume index); (c) 15 days absolute changes in QoL assessed by Minnesota Living With Heart Failure Questionnaire (MLHF); and (d) 15 days absolute and relative changes in prognostic biomarkers (N‐terminal pro‐B‐type natriuretic peptide ‐NT‐proBNP‐ and serum carbohydrate antigen 125‐CA125‐).

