### Study design

2.1

This study is designed as a multicenter, prospective, controlled, randomized, two‐arms, cross‐over, efficacy trial. The population includes patients with the diagnosis of stable HFpEF according to criteria of the European Society of Cardiology^18^ and New York Heart Association functional (NYHA) class II‐III/IV. A computer‐generated randomization sequence previously designed will be used to allocate participants (in a 1:1 ratio) to receive: (a) withdrawal of beta‐blocker followed by beta‐blocker reintroduction in two periods of 15 days; or (b) continuation of beta‐blocker followed by beta‐blocker withdrawal in two periods of 15 days. A summary of the study design is described in Figure 1. The study will be conducted in two centers in Spain. Discounting the time due to staggered entry, the total duration of a patient's follow‐up will be 6 months. All patients will provide signed informed consent before randomization. The research ethics committee approves the protocol of our center following the principles of the Declaration of Helsinki and national regulations.

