#### Eligibility assessment and screening visit

2.3.1

After reviewing the inclusion/exclusion criteria and signing the informed consent form, a comprehensive medical history, physical examination, anthropometry, and examination tests will be performed by two blinded cardiologists to patients' allocation groups. The examination tests will include an electrocardiogram (ECG), two‐dimensional transthoracic echocardiography, CPET, cognitive assessment by MMSE and MoCa, QoL assessment by MLHF, continuous ECG recording during the first 30‐day and blood samples for a panel of baseline biomarkers.

Finally, if the patients fulfill all the inclusion criteria (including ChI assessed by CPET) and any exclusion criteria (including a valid CPET without signs of ischemia), are randomized in a 1:1 ratio to one of the following interventions: (a) A‐arm: beta‐blockers withdrawal; or (b) B‐arm: beta‐blockers continuation.

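### With group meaning randomised arm, the planned repeated-measures ANOVA puts the withdrawal effect in the group-by-time term, which Section 2.6 describes as an effect of time

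*Protocol article*

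**What the plan says.** Section 2.1 of the protocol article calls the study a "multicenter, prospective, controlled, randomized, two‐arms, cross‐over, efficacy trial". One arm has "withdrawal of beta‐blocker followed by beta‐blocker reintroduction in two periods of 15 days"; the other has "continuation of beta‐blocker followed by beta‐blocker withdrawal in two periods of 15 days". At day 15 the first arm is off and the second on beta-blocker, and at day 30 the positions are reversed.

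The primary endpoint (Introduction) is "absolute and relative changes in peak oxygen uptake (peakVO2) at 15‐day after the intervention". The abstract adds that "PeakVO2 is assessed by cardiopulmonary exercise testing (CPET) at 15 and 30 days in both groups".

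For the analysis, Section 2.6 says that a repeated-measures ANOVA "will be used for the comparisons of continuous outcomes among the two‐intervention groups", and that the interaction of group with time-points "will be tested to unveil any effect of time (15 and 30 days) on the magnitude of the intervention". It does not say which term tests the primary hypothesis, or whether group is the randomised arm or the treatment received in a period.

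**The concern.** The description in Section 2.6 suits a parallel-group trial, in which each group keeps one treatment and the interaction asks whether the difference between groups grows or fades. Here the treatment changes sides between the two visits, so the same model terms mean something else. If group is the arm, the term that looks like the treatment comparison carries no treatment information, and the term that carries it is described as a time effect.

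What is at stake is the reading of the primary result. An analyst following the text could report no difference between the groups and then interpret a significant interaction as a benefit that fades or reverses by day 30, when withdrawal had worked equally well in both periods.

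**Working it through.** **1. What group means in the article.** The abstract speaks of both groups being tested at days 15 and 30, so a group persists across the switch. Section 2.3.1 says patients "are randomized in a 1:1 ratio to one of the following interventions: (a) A‐arm: beta‐blockers withdrawal; or (b) B‐arm: beta‐blockers continuation". Section 2.5 inflates 21 patients per group to 26 per arm. All three fit the randomised arm.

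**2. Expected means, group = arm.** Let μ be the mean on beta-blocker, τ the withdrawal effect and π the period effect.

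| | Day 15 | Day 30 |
|---|---|---|
| Arm A | μ + τ | μ + π |
| Arm B | μ | μ + τ + π |

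- Group effect: (A15 + A30)/2 − (B15 + B30)/2 = (2μ + τ + π)/2 − (2μ + τ + π)/2 = 0, for any τ.
- Group-by-time: (A15 − A30) − (B15 − B30) = (τ − π) − (−τ − π) = 2τ. With the 1.2 mL/kg/min of Section 2.5 this is 2.4.
- Baseline as a third time point, equal in both arms: both three-visit means are (3μ + τ + π)/3, so the group term is still 0. The treatment effect then sits in a 2-df interaction.
- Carry-over λ from withdrawal into arm A's second period: the group term becomes −(0) + λ/2 = λ/2 and the interaction 2τ − λ. For an assumed λ of 0.6 these are 0.30 and 1.8. The group term is thus a sequence and carry-over term.

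**3. Rejection rates.** Inputs from Section 2.5: 21 per arm, effect 1.2, SD 2.0, two-sided alpha 0.05. The correlation between visits is not given, so 0.3 to 0.7 is assumed. There were 20,000 simulated trials per row.

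| Correlation | Group term, τ = 1.2 | Group-by-time, τ = 1.2 |
|---|---|---|
| 0.3 | 5.2% | 89.3% |
| 0.5 | 4.9% | 96.6% |
| 0.7 | 4.9% | 99.8% |

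With τ = 0 both terms reject in about 5%. A hand check at correlation 0.5: the within-patient difference has SD 2.0 × √(2 × 0.5) = 2.0; the contrast has standard error 2.0 × √(2/21) = 0.617; and 2.4/0.617 = 3.89, which matches power near 97%.

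If the SD of 2.0 is instead read as the SD of change and the outcome SD is 2.8, the correlation is 1 − 2.0²/(2 × 2.8²) = 0.745. In 4,000 simulated trials the group term then rejected in 5.0% and the interaction in 96.9%.

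**4. Group = treatment received.** Let τ₁ and τ₂ be the withdrawal effects in the two periods, and s a chance difference in level between the arms.

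- Without carry-over, the group term is [(A15 − B15) + (B30 − A30)]/2 = (τ₁ + τ₂)/2, a valid treatment effect.
- Group-by-time is (A15 − B15) − (B30 − A30) = τ₁ − τ₂ + 2s + λ. Rearranged, it is (A15 + A30) − (B15 + B30), the sequence contrast itself. The data cannot separate its parts.

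**5. The plan's own figure.** The article gives no figure for this model. Its evaluable sample size of 42 serves here only as the setting. It is not reproduced from 1.2 and 2.0 alone (parallel arms need 59 per arm; a crossover with a difference SD of 2.0 needs 30 to 32 in total). That is a separate matter and nothing above rests on it.

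**The case against.** The strongest reply is that group may mean treatment received. Section 2.6 speaks of intervention groups, and Section 2.3.1 names the interventions as withdrawal and continuation, which are treatment states. On that reading the group term is the treatment effect, and without carry-over the interaction has expectation τ₁ − τ₂, which is what the text says it examines. This stands in part. A reader might infer that the stated interpretation is wrong on either reading; the documents do not support that. What remains is that the contrast is fully aliased with sequence and carry-over, so it cannot support the interpretation by itself. The wording elsewhere also points to the arm.

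A reader might also infer that the model omits a period term and is biased when losses are unequal. That does not follow. An ANOVA that tests group-by-time ordinarily includes time, and time-point here is period. Any bias figure would need an invented loss pattern and learning effect.

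Third, Section 2.6 never names the group main effect as the primary test, and the endpoint is set at 15 days after the intervention. A statistician could pick the correct contrast, which is in the model. This stands: a wrong conclusion is a risk, not something the plan fixes.

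Finally, this is a condensed article and no SAP is shown. Missing model detail is therefore not the complaint. The complaint is that the article states a meaning for a named term, and that meaning does not fit its own design.

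**Conclusion.** The point holds in this form. With group as the randomised arm, the group comparison over days 15 and 30 has expectation zero and rejects at about alpha, while group-by-time equals twice the withdrawal effect and is mislabelled as an effect of time. Those two results are algebra; they assume only equal arms by randomisation, no carry-over and the same withdrawal effect in both periods. The interaction's power of about 89% to 99.8% additionally assumes an effect of 1.2, SD 2.0 and a correlation of 0.3 to 0.7, none of which changes the conclusion. With group as treatment received, the main comparison is sound and only the interpretation of the interaction is unsupported.

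The trial's data can answer the primary question. The text leaves open which term does so, and its most natural reading points away from the right one. This should be settled before the analysis.

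**What to change.** Replace the ANOVA and interaction sentences of Section 2.6 with wording such as: *PeakVO2 at days 15 and 30 will be analysed with a crossover model having treatment in the period (withdrawn v on beta-blocker), period and sequence as fixed effects and patient as random effect. The primary test is the treatment contrast, reported with its 95% CI.* Delete the statement that the interaction shows an effect of time on the size of the intervention effect.

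Optionally, report the day-15 comparison between arms as a sensitivity analysis for carry-over. It does not cancel, but it gives up the crossover and has only about 47% to 49% power at 21 per arm with effect 1.2 and SD 2.0, so it is not a substitute for the primary test.

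The cost is a rewritten paragraph and a different model command. No extra patients, visits or measurements are needed. The article reports 28 of 52 patients enrolled and recruitment continuing, so the change could be made before the primary analysis.

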#### Cardiopulmonary exercise testing

2.4.1

Maximal functional capacity is evaluated with an incremental and symptom‐limited cardiopulmonary exercise testing (CORTEX Metamax 3B) on a bicycle ergometer, beginning with a workload of 10 W and increasing gradually in a ramp protocol at 10‐W increments every 1 minute. We define maximal functional capacity when the patient stops pedaling because of symptoms, and the respiratory exchange ratio (RER) is ≥1.05. During exercise, patients will be continuously monitored with 12‐lead electrocardiogram and blood pressure measurements every 2 minutes. Gas exchange data and cardiopulmonary variables are averaged every 10 seconds values. PeakVO2 is considered the highest value of VO2 during the last 20 seconds of exercise. The VE/VCO2 slope is determined by measuring the slope across the entire course of exercise.^20^ Each subject will undergo three tests (at baseline, 15 days, and 30 days).

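### Covariate adjustment is reserved for observed baseline imbalance; always adjusting the day-15 comparison for baseline peakVO2 would settle the model in advance and gain modest precision

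*Protocol article*

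**What the plan says.** The default analysis in Section 2.6 (Statistical plan) is: "A repeated‐measures analysis of variance (ANOVA) will be used for the comparisons of continuous outcomes among the two‐intervention groups". Its time points are the two post-randomisation visits: "The interaction group*time‐points will be tested to unveil any effect of time (15 and 30 days"). Adjustment is conditional: "Only in the event of imbalance in baseline characteristics, repeated‐measures analysis of covariance (ANCOVA) will be used".

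Three other places bear on this.

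- **Endpoint.** The Introduction states: "The primary endpoint of the study is absolute and relative changes in peak oxygen uptake (peakVO2) at 15‐day after the intervention". Section 2.5 words the null hypothesis in the same terms, as a change from baseline to 15 days.
- **Baseline measurement.** Section 2.4.1 (Cardiopulmonary exercise testing) states: "Each subject will undergo three tests (at baseline, 15 days, and 30 days"). A baseline peakVO2 is therefore planned for every patient, and a valid baseline exercise test is a condition of entry.
- **Design.** Section 2.1 describes a "multicenter, prospective, controlled, randomized, two‐arms, cross‐over, efficacy trial", so each patient is tested both on and off beta-blocker.

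**The concern.** The word that opens the conditional sentence excludes adjustment in every other case. This is a rule that the article lays down, not a detail that it leaves out. An analysis plan that always adjusted would contradict it.

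The rule rests on the wrong reason. Under randomisation any baseline difference between arms is due to chance, and Section 2.5 plans on that footing: "we assume no differences in peakVO2 at baseline among the two arms". That planning assumption is sound. But the case for a covariate is that it predicts the outcome, whether or not the arms happen to differ on it. The baseline value of the same measurement is the obvious candidate.

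Two things are at stake. The primary model is not settled until the baseline data have been inspected, which invites discretion. And if the primary comparison is the day-15 change between arms, some precision is given up for nothing.

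**Working it through.** **Inputs from Section 2.5.** Cross-sectional SD of peakVO2 2.8 mL/kg/min; mean change 1.2; common SD 2.0; 21 evaluable patients per arm; planned power 90%. On the test, the plan "assumes two‐sided testing at the 0.05 significance alpha level".

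**Assumptions.** The article does not say what the SD of 2.0 describes. It is taken here as the SD of the change, with 2.8 as the SD at both visits.

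**The plan's own figure.** With (1.960 + 1.282)² = 10.507:

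- Two-arm comparison, 1.2 and 2.0: 2 × 10.507 × 4 / 1.44 = 58.4, so 59 per arm, not 21.
- Paired, SD of difference 2.0: 10.507 × 4 / 1.44 = 29.2, so 30 in total, not 42.
- Paired, with 1.0 (10% of 10) in place of 1.2: 10.507 × 4 / 1.0 = 42.03, which matches the stated 42.

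The stated 42 is thus not reproduced from 1.2 and 2.0. That is a separate matter. It is shown because it leaves open which contrast the trial was sized for.

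**Implied correlation.** Var(change) = 2 × SD² × (1 − ρ), so ρ = 1 − 2.0² / (2 × 2.8²) = 1 − 4 / 15.68 = 0.745.

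**Day-15 between-arm comparison.**

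- ANCOVA residual SD = 2.8 × √(1 − 0.745²) = 1.87.
- Variance relative to the change score = (1 + ρ)/2 = 0.872, about 13% less.
- Holding the SD of change at 2.0, the ratio is 0.75 at ρ = 0.5 and 0.95 at ρ = 0.9, so 25% to 5% less.

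| Analysis | SD | n per arm for 90% power at 1.2 | Power, 21 per arm (t) |
|---|---|---|---|
| Change score | 2.0 | 59 | 48% |
| ANCOVA on baseline | 1.87 | 51 (44 to 56 for ρ 0.5 to 0.9) | 53% |

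The normal approximation gives 49% and 55%. A simulation of 40,000 trials (21 per arm, equal correlation between all visits) gives 47% and 52%. The gain is about five points of power whichever method is used.

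**Within-patient two-period contrast.** In the same simulation the standard error is 0.309 without baseline and 0.312 with it, and power is 96.6% and 96.1%. A single pre-randomisation value is common to both periods. When it is equally correlated with both, it carries no information about their difference.

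**The conditional rule.** Suppose it means testing baseline peakVO2 at 0.05 and using ANCOVA if the test is significant. ANCOVA is then triggered in about 5% of trials. With the change score as default, type I error is 4.7%. Power is 47%, against 52% for ANCOVA in every case. With unadjusted day-15 values as default, type I error is 3.6%.

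**How readily chance imbalance appears.** If 10 independent characteristics were each tested at 0.05, at least one would be flagged in 1 − 0.95¹⁰ = 40% of trials; with 20, in 64%. These counts are illustrative, as the article names no list.

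**The case against.** The strongest objection is that the design largely removes the need. This is a crossover, each patient serves as their own control, and for complete pairs the baseline adds nothing. Even for the day-15 comparison, the endpoint is a change, so baseline already enters. Both points stand, and they limit the precision argument to a modest gain on one reading of Section 2.6, which does not make clear which contrast is primary.

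Some stronger readings are tempting, but the article does not support them.

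- **A large loss of power.** Comparing raw day-15 values (SD 2.8) would give about 27% power, and ANCOVA would then have 55% less variance. But the endpoint and the null hypothesis are stated as changes, so raw values are not the fair comparator.
- **An inflated type I error.** A fixed rule looks at baseline data only and was slightly conservative in simulation. An analyst who ran both models and kept the better result would reach 6.7% (change score or ANCOVA) or 8.5% (raw values or ANCOVA). But Section 2.6 assigns one model to each condition and does not permit that choice.
- **A defect in the missing threshold and covariate list.** A condensed article may leave these to the full protocol or analysis plan. Only the stated condition is open to criticism.
- **A need to adjust for centre.** The article mentions no stratification by centre, so its text gives no basis for requiring it.

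What the objection leaves intact is the rule itself: imbalance is a poor reason to adjust, and its absence is a poor reason not to.

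**Conclusion.** The point holds in a limited form. Section 2.6 makes the choice of model depend on chance features of the baseline data and forgoes routine adjustment for a measurement that every patient provides. The harm is room for discretion and a modest loss of efficiency, not a biased or invalid test.

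For the day-15 between-arm change the loss is about 13% of variance, or roughly 48% against 53% power at 21 per arm and a difference of 1.2. This rests on reading 2.0 as the SD of change and 2.8 as the SD at both visits. The range is 5% to 25% of variance for correlations of 0.9 to 0.5. If the within-patient contrast in complete pairs is primary, there is no loss of precision, and the only benefit of a change is a model fixed in advance. This is a free improvement rather than the correction of a serious error.

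**What to change.** Delete the conditional sentence in Section 2.6 and name one primary model with no imbalance trigger:

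- If the day-15 between-arm change is primary, always include the baseline value of the outcome as covariate: baseline peakVO2 for the primary endpoint, and the corresponding baseline value for each continuous secondary endpoint.
- If the within-patient contrast is primary, use a crossover model adjusted for period.

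State which of the two is primary, since that decides whether baseline adjustment matters. The cost is one sentence. No new data are needed, because the baseline test is already scheduled for every patient. The change should be dated before outcome data are analysed; the article reports 28 of the planned 52 patients enrolled at January 14th, 2020.
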